- Hypoxemia occurrence rate (SpO2<90%): number of cases / total number of eligible participants

Secondary Endpoints

- Frequency of apnea (≥20 seconds)
- Degree of participant satisfaction (VAS)
- Intraoperative coordination (VAS)
- Adverse event occurrence rate

Exploratory Evaluation

- Comparison with capnography waveform
- Waveform analysis at the time of respiratory abnormality
- Consideration of respiratory abnormality-related risk factors (including obesity, age, history of smoking, drug administration dose, treatment duration and SAS).
  1. **Target Number of Participants and Study Period**

Safety Evaluation (Phase II): 45

Usefulness Evaluation (Phase III): 224 (112 in each group)

● Overall Duration: 24 months (from the initial announcement on the Japan Registry for Clinical Trials (jRCT) until August 31, 2021)

*Safety Evaluation (Phase II): 10 months (from the initial announcement on the jRCT until June 30, 2020)

Usefulness Evaluation (Phase III): 20 months (from January 1, 2020 until August 31, 2021)

● Registration Period: 18 months (from the initial announcement on the jRCT until February 28, 2021)

*Registration for Safety Evaluation (Phase II): 4 months (from the initial announcement on the jRCT until December 31, 2019)

Registration for Usefulness Evaluation (Phase III): 14 months (from January 1, 2020 until February 28, 2021)

- 1. **Institution Registration and Case Registration/Assignment Method**

Cases are registered centrally at the data center (Chiba University Hospital).

Case registration and assignment will be carried out in accordance with the following section.

- - 1. **Case Registration/Assignment Method**

● Safety Evaluation (Phase II)

1. Registration should take place, as a rule, within 14 days of obtaining consent.
2. The principal investigator or assistant investigators will obtain signed consent forms and confirm that participants satisfy the eligibility criteria, and that there is no conflict with the exclusion criteria. Registration forms should be filled in for participants who signed the consent form and sent it to the data center by fax or delivered it in person. The content of registration forms is verified at the data center, and eligibility assessment results are sent back by fax.
3. Patients who are registered once will not be removed from the database. When the same person is registered multiple times, the initial registration information (Registration No.) should always be used.

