The FAS will be all registered participants whose usefulness data is entered after randomization. However, those of them whose baseline data was not available and those who are seriously in bleach of the Study Protocol (no consent, registered outside the agreed period) will be excluded.

- - 1. **Per protocol set (PPS)**

PPS will be the population of FAS minus those cases that are seriously in bleach of the Study Protocol, in terms of research method or concurrent therapy.

1. Selection criteria violation
2. Exclusion criteria violation
3. Contraindicated drug violation
4. Contraindicated therapy violation
   - 1. **Safety analysis set (SAS)**

SAS will the registered patients who were fitted with the testing equipment (the monitor) at least once and underwent endoscopy under sedation.

- 1. **Target Number of Cases and Basis for Selection**

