**● Safety Evaluation (Phase II)**

In calculating the target number of participants for the safety evaluation cohort, with the expected value of 20% for hypoxemia (<90%), threshold at 40%, significance level of 0.05 on both sides and statistical power of 80%, required number is 43 cases. In consideration of drop-out, we set the target at 45 cases.

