Frequency of apnea (≥20 sec), degree of patients’ satisfaction and coordination during procedure will be evaluated with capnography group and nasal pressure monitor group, and the difference between those two groups will be analyzed using Pearson’s chi-square test. Significance level will be 0.05 on both sides, and confidence interval, and **two-sided 95% confidence interval will be computed.**

- - 1. **Safety Analysis**

Frequency of adverse event occurrence is the evaluation items to consider safety, therefore data table will be created. To estimate the proportion, exact 95% confidence interval for binomial distribution will computed for each group. Inter-group comparison will be carried out as required using Fisher's exact test.

- - 1. **Intermediate Analysis**

Data will be locked when registration of all cases for the Safety Evaluation (Phase II) is completed. The fixed analysis results will be disclosed to the independent data-monitoring committee (IDMC) (see 11.6) that oversees the study. The IDMC will evaluate the fixed data, and when they find the following situation, the study will be discontinued without carrying out registration for the usefulness evaluation.

- Rate of discontinued cases due to default accounted for 20% or more.
- Hypoxemia (SpO_2_<90%) was found in 60% or more of the cases.
- The IDMC determined that it will be inappropriate to conduct usefulness evaluation.

When the IDMC verified the safety, the participants will be registered for the usefulness evaluation. No intermediate analysis will be carried out in the usefulness evaluation.

- 1. **Independent Data-Monitoring Committee (IDMC)**

The independent data-monitoring committee (IDMC) will be established for this study. The IDMC will be independent of the people who conduct the study, and consist of two or more specialists whose position have no conflict of interest with this particular clinical study. The IDMC will provide appropriate advice and guidance in order to secure the safety of the participants and ethical and scientific soundness, based on the data monitoring protocol that is determined elsewhere for the purpose of securing safety of the participants. In cases where serious adverse events appear in this clinical study, the principal investigator may request the IDMC to deliberate concerning whether or not the study should be continued or revision of the Study Protocol. The IDMC will serve in writing the results of the deliberation to the principal investigator.

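### Phase II is sized as a test against a 40% hypoxemia threshold, but the only numeric hypoxemia criterion for not starting Phase III is 60%, and the lock and calendar do not fit the review that must come between

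*Protocol*

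**What the plan says.** **Sizing (Protocol 11.2, Safety Evaluation).** The calculation is done "with the expected value of 20% for hypoxemia (<90%), threshold at 40" per cent, with "significance level of 0.05 on both sides and statistical power of 80%, required number is 43 cases". The target is raised to 45 for drop-out.

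**Decision (Protocol 11.5.4).** The IDMC reviews the Phase II results, and Phase III registration does not go ahead on any of three grounds:
- discontinuation through default reaches 20%;
- hypoxemia "was found in 60% or more of the cases";
- the IDMC judges Phase III inappropriate.

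Phase III registration starts once the IDMC has verified safety. No interim analysis is planned within Phase III.

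**Lock and calendar.** Section 11.5.4 states: "Data will be locked when registration of all cases for the Safety Evaluation (Phase II) is completed". Section 11.5 instead places the Phase II analysis after all Phase II cases have completed the study. Section 5.3 closes Phase II registration on 31 December 2019, runs Phase II itself to 30 June 2020, and gives "Registration for Usefulness Evaluation (Phase III): 14 months (from January 1, 2020 until February 28, 2021".

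**The concern.** A sample size justified by a test implies that the test's result matters for what follows. Here the level and power belong to a comparison with 40%, while the rule that the protocol writes down is a different one at 60%. A reader of 11.2 would take it that Phase II gives strong protection against proceeding at a rate of 40%. The numeric criterion in 11.5.4 gives almost none at that rate.

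This is the only planned decision point before 224 patients are randomised with an unapproved device, so the IDMC should not be handed two figures with no stated relation.

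The timing is a second, separate matter. A lock at the end of registration can precede the last patients' procedures, and the calendar leaves no interval for the review that 11.5.4 itself requires.

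**Working it through.** **1. The plan's own sample size.** Inputs from 11.2: p0 = 0.40, p1 = 0.20, two-sided level 0.05, power 0.80. One-sample normal formula:

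n = [(z0.975·√(p0(1−p0)) + z0.80·√(p1(1−p1))) / (p0−p1)]²

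= [(1.960·√0.24 + 0.842·√0.16) / 0.20]² = [(0.960 + 0.337) / 0.20]² = 42.04, rounded up to 43.

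The stated figure reproduces, so the intended design is clear.

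**2. What that test requires at n = 45.** For an exact binomial test with 0.025 in the lower tail, the largest passing count is 11:
- P(X ≤ 11 | 0.40) = 0.0216
- P(X ≤ 11 | 0.20) = 0.826

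At 11/45 the exact 95% upper limit is 39.5%. At 12/45 it is 41.9%, so 12 or more events do not exclude 40%.

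**3. What the 60% criterion does at n = 45.** 0.60 × 45 = 27, so it is met when X ≥ 27.

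| True rate | P(X ≥ 27) |
|---|---|
| 20% | <0.01% |
| 40% | 0.5% |
| 47% | 5.5% |
| 50% | 11.6% |
| 55% | 30.2% |
| 60% | 56.4% |
| 70% | 94.5% |

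The 47% row is the top of the range cited in 11.2 (12–47% under propofol). With 43 evaluable patients (X ≥ 26) the values are nearly the same: 0.5% at 40%, 5.3% at 47%, 11.1% at 50% and 54.1% at 60%.

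**4. The gap between the two.** Counts from 12 to 26 fail the test that sized Phase II and leave the 60% criterion unmet. At a true 40% this happens with probability 97.8% − 0.5% = 97.3%. At the upper end, 26/45 is 57.8% with an exact 95% confidence interval of 42.2% to 72.3%. The whole interval lies above 40%, and the criterion is still not met.

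**5. Timing, side by side.**
- Section 5.6: patients are registered before entering the treatment room. When the last patient is registered, that patient's hypoxemia outcome does not yet exist.
- Section 7.1, note b: Phase II monitoring records are analysed to three hours after treatment.
- Section 8.5: adverse events are collected to the day after last use of the equipment, and serious ones to seven days. A patient registered and treated on 31 December 2019 would still be in the serious-event window until about 7 January 2020.
- Section 11.5.4: lock at the end of registration. Section 11.5: analysis after completion in all cases.
- Section 5.3: Phase III registration from 1 January 2020, the day after Phase II registration closes. That leaves no days for lock, analysis and IDMC review.
- Section 7.1, note b also lets Phase II findings change the Phase III observation period, another reason for Phase II results to be complete first.

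**The case against.** The strongest reply is that the 60% figure is one automatic harm bound within a wider gate. The IDMC may stop on its own judgement (repeated in 14.1), must have verified safety before Phase III registers anyone, and a 20% default rate also stops. It works under a data monitoring protocol held elsewhere, and Phase II analysis details are left to the SAP. A harm bound and a success test used for sizing can coexist.

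Most of this stands. A reader might infer that the gate as a whole rarely stops, or that a device with a true 40% rate simply goes on to randomisation. The documents do not support that: the probabilities above concern the numeric criterion only. Nor can it be said that no decision anywhere uses the 40% test. What can be said is that the protocol fixes both figures and links them nowhere.

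Three further inferences should be resisted:
- **That 40% is an unacceptable rate.** The protocol calls it a threshold, and it lies inside the cited 12–47%.
- **That the lock date makes stopping rare.** It does not; the results at n = 43 and n = 45 barely differ.
- **That Phase II lacks an analysis set.** Section 11.5, under the Phase II heading, names the FAS, defined as "all registered participants whose usefulness data is entered after randomization", and Phase II has no randomisation. But that sentence speaks of the usefulness evaluation and recurs under Phase III, so it reads as carried-over text. The safety analysis set in 11.1.3 already covers monitored and sedated Phase II patients.

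On the calendar, 11.5.4 still makes Phase III registration conditional on the IDMC, so the dates do not override the gate. They conflict with it and need aligning.

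**Conclusion.** The point holds in limited form. The 80% power and 5% level in 11.2 do not describe the numeric hypoxemia criterion in 11.5.4. That criterion is met with probability 0.5% at a true 40%, 11.6% at 50% and 56% at 60%, and it leaves results from 12 to 26 of 45 in a range the protocol does not address. Separately, the lock wording in 11.5.4 conflicts with 11.5 and with registration before the procedure, and 5.3 leaves no time for IDMC review.

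The figures assume 45 evaluable patients, independent binomial outcomes and an exact test at 0.025 in the lower tail. They say nothing about how the IDMC would use its discretion.

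This should be fixed before Phase II closes, but it does not undermine the main conclusion: Phase III rests on a concurrent randomised comparison, which this gate does not bias.

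**What to change.** **Reconcile 11.2 and 11.5.4**, with the choice of bound left to the sponsor and the IDMC. One of two routes will do:
- tie the IDMC decision explicitly to the comparison with the 40% threshold; or
- keep the 60% criterion, state that the 80% power does not apply to it, and give its stopping probabilities as tabulated above.

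The first route is a real trade-off and is not prescribed here. If proceeding required 11 or fewer events of 45, the chance of not proceeding would be 17% at a true 20%, 45% at 25% and 74% at 30%.

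**On either route:**
- report the Phase II hypoxemia rate to the IDMC with its exact 95% confidence interval, set against 40%;
- lock Phase II data after the last Phase II patient has completed observation and the adverse-event and serious-adverse-event reporting window, and align 11.5 and 11.5.4;
- in 5.3 and the Study Outline, make the start of Phase III registration depend on the IDMC's decision instead of a fixed 1 January 2020;
- optionally, delete the carried-over FAS sentence under the Phase II heading in 11.5. No new analysis set is needed.

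The cost is amendment wording and a short gap between the phases.
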